Specific Aim 2 seeks to compare the satisfaction of patients between groups as measured by self-reported satisfaction questionnaires. The data will be collected using ordered, multi-point Likert scales, and in some cases responses will be dichotomized (e.g. 5 points with 1-3 vs 4-5). For a power/sample size estimate, we used a difference in proportion estimate. Using a likelihood ratio, chi-squared test of two proportions,  $\alpha = 0.05/3 = 0.016$ , power=0.80 and an underlying referent satisfaction of 80% and equal sample sizes of 92-115/arm per above, we are able to detect minimum differences in proportions of 15 percentage points, and minimum detectable odds ratios 4.9. To compare the quality of life metrics of patients between groups as measured by SF-12,® the data will be collected using SF-12® and appropriately converted to a bounded value between 0 and 1. In analyses, we will use the inverse normal transformation of quality of life to obtain a normally distributed quality of life value. For a power/sample size estimate, we estimated the difference in score, using a two-sample *t* test with pool variance of 0.09, the Delta Method and Taylor Series expansion, properties of the inverse normal transformation,  $\alpha = 0.05/3 = 0.016$ , power=0.80, and equal sample sizes of 92-115/arm per above. We are able to detect a minimum difference in quality of life scores of 0.09 (e.g. 0.50 vs 0.59 would be detectable, on a scale from 0-1).

Cost-effectiveness (Specific Aim 3) analyses use aggregate cost and effectiveness values, along with confidence intervals derived from a bootstrap method. Therefore, sample size meeting the criteria for the above two aims would be sufficient for Specific Aim 3. Missing data will be mitigated through retention strategies (see Section C.8) and augmentation with EHR data (see Section C.5.3). For patients missing some, but not all, follow-up data, the missing data mechanism will be explored and modern imputation methods such as multiple imputations will be used to impute missing covariates following satisfaction of the method's assumptions.

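### The quality-of-life difference of 0.09 called detectable in 6.2.b does not follow from the variance, alpha, power and sample size stated with it, whichever scale the variance is on

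*Protocol*

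**What the plan says.** Protocol 6.2.b (Power and Sample Size) sets the number of patients from HbA1c: 92 per arm, raised to 115 per arm for 20% attrition, 345 in all. It then works out what this number can detect for Specific Aim 2.

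For quality of life, the SF-12 is converted to a value between 0 and 1. For the analysis, "we will use the inverse normal transformation of quality of life to obtain a normally distributed quality of life value". The calculation is described as "using a two-sample *t* test with pool variance of 0.09, the Delta Method and Taylor Series expansion", with alpha 0.05/3 given as 0.016, and "power=0.80, and equal sample sizes of 92-115/arm per above". The result is: "We are able to detect a minimum difference in quality of life scores of 0.09", with 0.50 versus 0.59 as the example.

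The section does not say whether the variance of 0.09 describes the raw 0-1 score or the inverse-normal score, gives no source for it, and does not state whether the test is one- or two-sided.

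**The concern.** The paragraph supplies every number that a detectable difference needs, so the result can be checked. A pooled variance of 0.09 is a standard deviation of 0.30, so a difference of 0.09 is a standardized difference of 0.30 on the raw scale. That is small for about 100 patients per arm at alpha 0.016.

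The figure matters in three places. Section 6.2.b counts patient-centered outcomes among the primary analyses. Section 2.3.b has two quality-of-life hypotheses comparing the exercise arms. Section 6.2.b also calls the sample size sufficient for Aim 3 because it meets the criteria of Aims 1 and 2, and Aim 3 uses quality of life as one of its effectiveness measures. A reader who takes 0.09 at face value will misjudge what a null quality-of-life result can exclude.

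**Working it through.** **Inputs (Protocol 6.2.b).** Pooled variance 0.09, so SD = √0.09 = 0.30; alpha 0.016; power 0.80; n = 92 or 115 per arm, equal arms. Two-sided testing is assumed.

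**Formula.** Detectable difference = (z for 1 − α/2 + z for power) × SD × √(2/n). Here 2.409 + 0.842 = 3.251. With the noncentral t in place of the normal, the detectable standardized difference d is 0.483 (n = 92) and 0.431 (n = 115).

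**Attempt to reproduce 0.09, variance on the raw 0-1 scale.**
- n = 92: 3.251 × 0.30 × √(2/92) = 0.144; noncentral t, 0.145.
- n = 115: 3.251 × 0.30 × √(2/115) = 0.129; noncentral t, 0.129.
- By the delta method at 0.50, the SD on the inverse-normal scale is 0.30/0.399 = 0.752. Then Φ(0.483 × 0.752) − 0.5 = 0.142 and Φ(0.431 × 0.752) − 0.5 = 0.127.
- Power for a difference of 0.09: 34.8% (n = 92) and 44.1% (n = 115).
- Patients needed for 0.09 at 80% power: 2 × (3.251 × 0.30/0.09)² ≈ 235 per arm (236 by the t calculation).

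**Attempt to reproduce 0.09, variance on the inverse-normal scale.**
- From 0.50: Φ(0.483 × 0.30) − 0.5 = 0.058 (n = 92); Φ(0.431 × 0.30) − 0.5 = 0.051 (n = 115).
- 0.50 versus 0.59 is a shift of 0.2275 on this scale, or 0.2275/0.30 = 0.76 SD. Power is 99.6% (n = 92) and above 99.9% (n = 115).

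**Other readings.**

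| Reading | n = 92 | n = 115 |
|---|---|---|
| Raw, alpha 0.05/3 unrounded, two-sided | 0.144 | 0.129 |
| Raw, alpha 0.016, one-sided | 0.133 | 0.119 |
| Raw, alpha 0.05, two-sided | 0.125 | 0.111 |
| Raw, alpha 0.05, one-sided | 0.110 | 0.099 |
| 0.09 taken as the SD, raw | 0.043 | 0.039 |
| 0.09 taken as the variance of a between-patient difference (factor 2 dropped) | 0.102 | 0.091 |

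Only the last row comes close, and there only at 115 per arm. It is not a pooled variance, which is what the protocol names.

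**What variance would give 0.09?** On the raw scale, (0.09/0.483)² = 0.035 to (0.09/0.431)² = 0.044. On the inverse-normal scale, (0.2275/0.483)² = 0.22 to (0.2275/0.431)² = 0.28. The stated 0.09 lies between the two ranges and fits neither.

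**The case against.** The strongest reply is that low power has not been shown. The planned analysis is on the transformed scale, the variance is listed beside the transformation, and a raw SD of 0.30 is slightly more than that of scores spread evenly over the whole 0-1 range (√(1/12) = 0.289). If the variance is a transformed-scale one, the protocol understates its sensitivity. This stands as far as it goes: a reader might infer that the quality-of-life comparison has only 35% to 44% power, and the protocol does not establish that.

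Two things still favour the raw scale. The delta method is what carries a raw variance to a transformed scale, and would not be needed for the test if the variance were already there. The HbA1c calculation in 6.2.b works in the same direction, deriving the SD of log HbA1c from the raw SD and mean. These make the raw reading likelier, not certain. Neither reading rescues 0.09.

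A reader might also infer the cause, for example that two arms of 115 were entered as 230 per arm. That is algebraically the same as dropping the factor of 2 or mislabelling a variance, so the document cannot tell these apart. A further inference, that the transformation breaks down at scores of exactly 0 or 1, depends on a form of the transformation that the protocol does not fix.

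Finally, HbA1c set the sample size; the quality-of-life figure was calculated back from it. This is correct and limits the consequence to how Aim 2, and the quality-of-life part of Aim 3, are interpreted.

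**Conclusion.** The stated detectable difference of 0.09 is wrong as written. From the protocol's own inputs, with two-sided testing, it is about 0.13 to 0.145 if the variance is on the raw 0-1 scale and about 0.05 to 0.06 from a score of 0.50 if it is on the inverse-normal scale. The corresponding power for the protocol's example of 0.50 versus 0.59 is about 35% to 44%, or above 99%. The raw reading is better supported by the wording, but the scale is not stated, so the conclusion is that the figure cannot be reproduced, not that the comparison is underpowered. The sample size justification for HbA1c is not touched by this point.

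**What to change.** In Protocol 6.2.b, state which scale the variance of 0.09 is on and where it comes from, and state the sidedness of the test. Then restate the detectable difference (or the power for 0.09) to match:
- raw 0-1 scale: 0.145 with 92 per arm to 0.13 with 115 per arm, or power of about 35% to 44% for 0.09;
- inverse-normal scale: 0.058 to 0.051 from 0.50, or power above 99% for 0.50 versus 0.59.

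If the variance itself proves to be misstated, correct it and recompute. Report the quality-of-life comparison with its confidence interval and interpret it against the restated figure.

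The cost is a few sentences of text and one recalculation. No change in enrolment or in the planned analysis method is needed. If the raw scale is confirmed, the sponsor accepts a less favourable stated sensitivity.

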### **Modifiable Activity Questionnaire, Block Food Frequency Questionnaire, SF-12 Health Survey, Exercise Barriers and Benefits Scale**

The following portion of the baseline visit involves a series of test, surveys, and questionnaires. The potential participant must complete all of the tools in order to proceed.

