## **6.2 DATA ANALYTICAL METHODS**

### **6.2.a DATA ANALYSIS PLAN**

Statistical analyses will investigate clinical effectiveness of structured physical activity regimens across varying frequencies. The main statistical approach will be to date-match outcomes to concomitant exercise regimens, then to examine univariate and multivariate associations with changes in clinical outcomes, patient-centered outcomes, and cost. Statistical significance will be determined at  $P < 0.01$ , a stricter value due to the expected number of models used, or with other adjustments for multiple comparisons when applicable. Statistical analyses will be performed using SAS® (Cary, NC), and supplemented with STATA or Splus for methods not available in SAS®.

Study participants who are not able or willing to continue with the randomized frequency of intervention will be treated as loss to follow-up and only data obtained while in the assigned protocol will be used in the primary analysis (intention-to-treat). Since participants and non-participants continue to receive care within the healthcare system contemporaneously during the research study, IMPACT will obtain interstitial outcome data and complete clinical narrative through observational data available in the EHR. The statistical analysis will be conducted by Senior Statistician/s with the guidance of Biostatistical Consultant [name].

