### **Statistical Analysis**

In univariate analyses, the percent change from baseline will be compared across intervention arms using appropriate parametric (ANOVA, *t* tests) or non-parametric (Wilcoxon) methods.

In multivariate analyses, change in outcomes will be modeled using linear regression. Percent change from baseline will be a continuous outcome with intervention arm as the predictor of interest and various participant characteristics as covariates (e.g. sex, age, race/ethnicity, anthropometry, self-reported diet and exercise, pharmacotherapy, family history, etc.). Repeated measures analysis using the outcome at different time points and mixed-effects models will also be performed. Available nonparticipants will serve as contemporaneous comparators to address possible secular trends in outcome values.

Study participants in the exercise program may also be undergoing concomitant pharmaceutical therapy to reduce HbA1c. The approach is to repeat the above analyses stratified by use of hypoglycemic medication. Another approach is to use a composite binary outcome variable for whether participants were successful in either decreasing diabetes medication or reduced HbA1c by 0.5% without increasing medications. Logistic regression will be used to assess the likelihood of achieving the composite outcome.

Study participants will be studied based on their randomized assignment (intention-to-treat). In sensitivity analyses, participants may be re-analyzed based on actualized attendance if they more closely resemble one of the other arms (once-weekly, thrice-weekly, usual care). A study participant assigned to thrice-weekly, who attends only once a week may be re-analyzed as a weekly patient. Stratification by adherent (attendance >80%) or not will also be another sensitivity analysis.

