## **6.2.b POWER AND SAMPLE SIZE**

The primary analyses for this study will be comparing the clinical outcomes, patient-centered outcomes, and cost effectiveness of structured exercise regimens across varying frequencies (once vs. thrice-weekly, compared to usual care). For Specific Aim 1, overall change in baseline of outcome values will be examined (e.g. HbA1c, VO2max, physical activity). By the algebraic properties of log and variance, we estimated difference in groups as  $\log(\text{HbA1c}_1) - \log(\text{HbA1c}_2) = \log(\text{HbA1c}_1 / \text{HbA1c}_2)$ , and  $\text{SD}(\log(\text{HbA1c})) = \text{SD}(\text{HbA1c}) / \text{mean}(\text{HbA1c})$ . A two-sample *t*-test between means, Bonferroni adjusted  $\alpha = 0.05/3 = 0.016$ , assuming normality of  $\log(\text{HbA1c})$ , equal group variances, and a baseline mean HbA1c of 6.5%, we will have 80% power to detect a 0.5% point difference in HbA1c with 92 patients/arm. Accounting for a 20% attrition, this will require 115/arm, 345 patients total.

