#### Secondary Data Sources

Secondary data sources are existing datasets collected by another entity. The IMPACT Study will use EpicCare EHR to obtain HbA1c results and other metabolic measurements if participants do not attend their study visits.

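### Multiple imputation is aimed at covariates and not at HbA1c, so the change-from-baseline analyses use observed cases only and ignore earlier HbA1c values, although 20% attrition is planned

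*Protocol*

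**What the plan says.** Protocol 6.2.b (Power and Sample Size) sets the attrition allowance: "Accounting for a 20% attrition, this will require 115/arm, 345 patients total".

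The same section then deals with missing data in two steps.
- The first is prevention and recovery: "Missing data will be mitigated through retention strategies (see Section C.8) and augmentation with EHR data (see Section C.5.3"). The table of contents lists no sections with those numbers.
- The second is the statistical method. The technique named there is aimed at covariates: "modern imputation methods such as multiple imputations will be used to impute missing covariates following satisfaction of the method's assumptions". Its scope is patients with partial follow-up, as the opening of that sentence shows: "For patients missing some, but not all, follow-up data, the missing data mechanism will be explored".

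Protocol 6.2.a, Study Aim 1, Statistical Analysis lists ANOVA, *t* or Wilcoxon tests on percent change from baseline. Then: "In multivariate analyses, change in outcomes will be modeled using linear regression". Repeated-measures and mixed-effects models follow as further analyses. No model is labelled primary. The same section says participants are studied by randomised assignment.

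Three other places decide which HbA1c values exist and count.
- 9.1.a (Secondary Data Sources) uses the EHR to "obtain HbA1c results and other metabolic measurements if participants do not attend their study visits".
- 8.3.a (Early Discontinuation of Treatment) says follow-up assessments are obtained for removed participants.
- 6.2.a (opening) says that those who stop the assigned frequency "will be treated as loss to follow-up and only data obtained while in the assigned protocol will be used in the primary analysis".

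**The concern.** The quantity that the plan expects to lose is follow-up HbA1c. The one imputation method named is pointed at something else, and patients with no follow-up at all fall outside its sentence.

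A test or regression on change from baseline to a visit can include only patients with an HbA1c at that visit. A patient seen at month 3 and lost before month 6 contributes nothing to the 6-month comparison, although the month-3 value was scheduled and collected (4.1.b). The result describes patients with an observed outcome, whereas Aim 1 promises an analysis of everyone as randomised.

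If leaving is related to early HbA1c response, and differently by arm, the between-arm difference is biased. Differential leaving is plausible: allocation is open, and attendance ranges from no sessions to three a week (2.2.a). Covariate imputation does not correct this.

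**Working it through.** **1. The plan's own figure.** Evaluable patients per arm (6.2.b): 92. Attrition: 20%. 92 / (1 − 0.20) = 115 per arm, and 3 × 115 = 345, so the stated total reproduces. The plan expects 115 − 92 = 23 patients per arm, 69 in total, without an evaluable outcome. The power rests on the 92.

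**2. Who enters each analysis**

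| Patient | Change-from-baseline tests and regression at month 6 | Mixed-effects repeated measures |
|---|---|---|
| HbA1c at months 3 and 6 | in | in |
| Month 3 only, EHR supplies month 6 | in, if the 6.2.a opening rule allows the value | in, same condition |
| Month 3 only, no month-6 value from any source | out; month 3 unused | in; month 3 used |
| Baseline only | out | in, if baseline is one of the modelled visits |

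Imputing covariates moves nobody from out to in.

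**3. Possible size of the bias.** The protocol gives no SD and no dropout pattern, so this is an illustration under assumptions.
- From the plan: 0.5-point effect at 6 months, 115 per arm, 20% attrition.
- SD of change: back-solved on the raw scale from 92 per arm, α = 0.016 (two-sided assumed) and 80% power. SD = 0.5 / [√(2/92) × (2.409 + 0.842)] = 0.5 / (0.1474 × 3.251) = 1.04. The simulation used 1.05.
- Assumed: correlation 0.6 between 3- and 6-month change; 0.35-point effect at month 3; all attrition after month 3; log-odds of leaving rising by 0.5, 1.0 or 1.5 per HbA1c point of poorer 3-month change.

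Mean observed-case estimate of the true 0.50:

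| Where leaving depends on 3-month change | EHR recovery | 0.5 / 1.0 / 1.5 |
|---|---|---|
| Exercise arm only, 20% leave | none | 0.57 / 0.61 / 0.65 |
| Exercise arm only, 10% leave | none | 0.53 / 0.56 / 0.58 |
| Exercise arm only, 20% leave | half, at random | 0.53 / 0.55 / 0.56 |
| Exercise arm, half as strong in usual care | none | 0.53 / 0.55 / 0.55 |
| Both arms equally | none | about 0.50 |
| Usual care only | none | 0.43 / 0.38 / 0.36 |

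Relative to 0.50, the first row is an overstatement of about 13% to 30% (0.566 / 0.50 = 1.13; 0.650 / 0.50 = 1.30). Recovering half the missing values brings this to about 6% to 13%. The last row is an understatement of about 13% to 29%. A re-run of these scenarios gave the same pattern to within about 0.01.

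An estimate that also uses the month-3 value returns 0.50, with an SE of about 0.151 against 0.157. The gain in precision is small; the argument rests on bias.

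**The case against.** Much can be said for the plan.

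**Covariates.** A reader might infer that the imputation has almost nothing to do, because at baseline "The potential participant must complete all of the tools in order to proceed". The protocol does not support that. The sentence concerns patients with partial follow-up, so it can cover follow-up covariates: activity, diet and anthropometry are repeated at every later visit (4.1.b), and adherence is a covariate (Aim 1). Pharmacotherapy and family history are also listed, and no entry step shown secures them.

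**Recovery of HbA1c.** A reader might call these pure completer analyses. That is also too strong. EHR values fill missed visits (9.1.a), removed participants are still assessed (8.3.a), and every participant must have a primary care physician in the health system (2.4.c). The missing fraction may fall well below 20%. It will not be zero: back-fill needs a clinic value to exist, and the opening rule of 6.2.a may bar values obtained off the assigned regimen.

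**Ranking of models.** No model is called primary, so the regression cannot be presented as the declared main analysis. The mixed model is already planned, and ranking methods is often left to a statistical analysis plan. But the protocol does state an imputation target, and it is not the outcome that attrition removes.

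**Size and direction.** It is tempting to say that the exercise effect is overstated by 13% to 30%. That needs response-dependent leaving in the exercise arm only and no EHR recovery. The opposite sign is possible: 8.3.a removes anyone in any arm who starts insulin, which could take poorly controlled patients out of usual care. Also, the month-3 estimate returns 0.50 by construction, because leaving was made to depend only on that observed value. The simulation uses absolute change, whereas the regression uses percent change.

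**Conclusion.** The point holds in this form. As written, the change-from-baseline tests and linear regression are observed-case analyses after EHR substitution. They ignore earlier HbA1c values, and no imputation is named for HbA1c that remains missing. This sits badly with 20% planned attrition and with analysis by randomised assignment.

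Neither the size nor the direction of bias can be fixed from the protocol. The illustrations run from about −29% through zero to about +30% of a 0.5-point effect, and about +6% to +13% if dependence is in the exercise arm only and the EHR recovers half. These rest on an assumed SD, correlation, month-3 effect and dropout mechanism. The smaller shifts, 0.53 to 0.56, lie well within one SE (0.157) of 0.50.

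This is a worthwhile and cheap improvement, not a demonstration that the planned result would be wrong.

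**What to change.** - **6.2.a, Aim 1.** Name the already planned mixed-effects repeated-measures model as the primary HbA1c analysis. Include all randomised participants with any HbA1c, with baseline and every scheduled visit (3, 6, 12, 18 and 30 months), and arm-by-visit contrasts at the end of Phase 1 (month 6) and Phase 2 (month 30). Keep the linear regression as supportive.
- **6.2.b.** Extend imputation from missing covariates to HbA1c still missing after EHR back-fill, by arm, using baseline and earlier HbA1c. Say how patients with no follow-up are handled.
- **Reconcile** the opening of 6.2.a, 6.2.b, 8.3.a and 9.1.a on which observed HbA1c values enter the primary analysis, including EHR values and assessments made after leaving the assigned regimen.
- **Optional:** a sensitivity analysis that imputes missing exercise-arm outcomes from the usual-care arm.

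The cost is protocol or analysis-plan wording and modest programming. No visit or measurement is added and the stated sample size is unchanged. The estimate may prove less favourable to exercise than the observed-case regression. The mixed model relies on missingness being explained by the data in the model.

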## 7.2 PROTECTION AGAINST RISK

### 7.2.a STAFF TRAINING

[name] (PI) will monitor completion of regulatory documentation, including approval of the protocol and Informed Consent forms by the Stanford Institutional Review Board (IRB) and certification that each member of the study team has complied with regulations for Protection of Human Subjects training and HIPAA. The IMPACT Study will not be performed until an appropriate IRB submission and consent form unique to this study has been

approved. All examination procedures pose little risk to participants. However, research staff members are trained to respond to all health emergencies by first contacting the emergency response system (9-1-1), then notifying appropriate medical personnel on-site. In addition, the Principal Investigator will supervise the training of clinic staff in human subjects certification, informed consent and assent procedures, and the collection of data.

